## Abstract

**Background:**

The diagnosis and treatment of cancer is a major life stress such that approximately 35% of patients experience persistent clinically significant distress and carers often experience even higher distress than patients. This paper presents the design of a two arm randomised controlled trial with patients and carers who have elevated psychological distress comparing minimal contact self management vs. an individualised tele-based cognitive behavioural intervention.

**Methods/design:**

140 patients and 140 carers per condition (560 participants in total) will been recruited after being identified as high distress through caller screening at two community-based cancer helplines and randomised to 1) a single 30-minute telephone support and education session with a nurse counsellor with self management materials 2) a tele-based psychologist delivered five session individualised cognitive behavioural intervention. Session components will include stress reduction, problem-solving, cognitive challenging and enhancing relationship support and will be delivered weekly. Participants will be assessed at baseline and 3, 6 and 12 months after recruitment. Outcome measures include: anxiety and depression, cancer specific distress, unmet psychological supportive care needs, positive adjustment, overall Quality of life.

**Discussion:**

The study will provide recommendations about the efficacy and potential economic value of minimal contact self management vs. tele-based psychologist delivered cognitive behavioural intervention to facilitate better psychosocial adjustment and mental health for people with cancer and their carers.

**Trial Registration:**

ACTRN12609000301268.

## Background

### The mental health burden of cancer

It is estimated that from 2001 to 2011 the number of newly diagnosed cases of cancer will increase by 29% in women and 32% in men [1]. Cancer is the leading cause of burden of disease and injury in Australia, accounting for nearly one-fifth of the total disease burden [2]. The diagnosis and subsequent treatment of cancer is a major life stress that is followed by a range of well described psychological, social, physical and spiritual difficulties [3]. While over time most people diagnosed with cancer go on to adjust effectively to their changed life circumstances without clinical intervention, approximately 35% will experience persistent clinically significant distress such as anxiety and depression, adjustment disorders, fears about cancer recurrence, and post traumatic stress reactions, that for some will worsen over time [4,5]. As well, many partners of cancer patients report high levels of psychological distress, sometimes even greater than that of the patients [6,7]. The most powerful prospective predictor of longer term distress is current distress [8,9], hence there is a clinical imperative to identify patients and family members experiencing high distress and refer those people to accessible targeted psychosocial therapies [10].

A range of measures are available to screen for high psychosocial distress. Memorial Sloan Kettering Cancer Center, New York developed a simple single item Brief Distress Thermometer (BDT) and accompanying Problem Checklist [11] that has now been incorporated into clinical practice guidelines for psychosocial care after cancer and relevant consumer materials [12,13]. The BDT is free of charge; and easy to administer and interpret; and has comparable accuracy with longer distress screening instruments such as the 14 item Hospital Anxiety and Distress Scale and the 18 item Brief Symptom Inventory [14,15]. As such, the BDT is well suited for large-scale and repeated distress screening. There is also a well-established body of evidence demonstrating that psychosocial interventions increase wellbeing, improve adjustment and coping and reduce psychological distress in people affected by cancer [10,16]. A range of effective intervention approaches have been described using varying delivery formats, and these include cognitive behavioural therapy, relaxation techniques, psycho-education, supportive psychotherapy, and family and couples therapy. As well, in North America and Australia clinical practice guidelines for psychosocial care have been developed that provide recommendations for intervention [10,12,13,17]. However, despite the availability of guidelines and tools, evidence-based psychosocial care is the exception rather than the norm. Clinicians tend to overlook patients' psychosocial needs, often do not recognise depression and other psychiatric illnesses in their patients, and have limited response skills for managing patients' distress [8,18-21]. Routine screening for psychological distress is uncommon in acute treatment centres reducing the likelihood of detecting highly distressed patients and providing them with timely support [8]. Compounding this, while *some *psychosocial care is likely to be delivered to patients at diagnosis, it is uncommon at the time of treatment completion and will seldom include family members. For example, in a sample of 439 cancer patients treated at a tertiary cancer centre in Queensland, psychosocial care information was provided to only half of patients at diagnosis, and at the completion of treatment to less than one third [21]. Psychosocial care services that are responsive and accessible across the illness experience and beyond the acute treatment setting are urgently needed.

### Community-based approaches to psychosocial intervention

Increasingly, community based non-government organisations have taken on a role as providers of support services for cancer patients and their families. The most prominent and easily accessed of these are tele-based information and support services or helplines that are now available in the UK, Netherlands, Australia and North America [22-25]. Cancer helplines provide a potential assessment and referral point for patients and family members for psychosocial intervention both during and beyond their treatment experience within the acute health care setting. In Australia the Cancer Council Cancer Helpline is provided through a national toll free number ([name]) and managed by each state Cancer Council. Telephone delivery provides a broad reach that addresses barriers to access such as geography, ill health, and cost. The Helpline service is staffed by nurses and allied health professionals who have experience and/or qualifications in oncology and who undergo additional training in psycho-oncology and decision support [26,27]. Helpline operators provide brief cancer information and emotional support typically in a single contact that includes an average of 8 minutes of verbal contact time followed by mailed written patient education materials. The service is underpinned by a constantly updated and extensive data base of community and hospital based services to facilitate referral across sectors. The use of a centralised call centre enables standardisation of procedures to be easily achieved with constant quality assurance, outcome monitoring and data collection built into the operational system. Policies and procedures to address issues such as confidentiality and duty of care are in place and are consistent with Australian Psychological Society professional standards and medicolegal obligations [28].

With regards to psychosocial intervention, population-based approaches need to address not only access, but also the costs of delivery that may impede dissemination. For example, individualised cognitive behaviour therapy has been found in meta-analyses to reduce anxiety and depression after cancer with follow up periods of up to eight months [29]. While these results are impressive, this approach will require specialist psychological staff, infrastructure to support delivery, and compliance by patients with routinised therapy sessions. In comparison, minimal contact approaches to psychological care with the use of self management materials for people with sub-threshold depression have been found to reduce the later incidence of major depression in patients in primary care [30]. Efficacious self management has been defined as where individuals are able to monitor their own condition and undertake the necessary cognitive, behavioural and emotional responses to effect a satisfactory quality of life [31]. Self management interventions have been shown to have consistent positive effects on mood across a range of chronic illnesses [31] and so have great potential as a cost effective method of providing psychological support to people affected by cancer. Proposed advantages of self management approaches are equity, accessibility and choice [32]. However, it is not yet clear for which distressed patients a minimal contact approach would be efficacious, and for whom more in depth individualised approaches are necessary. For example, it may be that patients and carers with borderline distress will return to pre-morbid functioning with minimal contact approaches while clinically distressed people will require more in depth care to achieve similar benefits. This is a research question that is of critical importance in order to guide the cost-effective delivery of psychosocial oncology care services for the population.

For practical capacity for immediate translation into the community, psychosocial distress screening and intervention should be nested within an available service infrastructure. The Cancer Helpline provides a unique service infrastructure with demonstrated feasibility for the delivery of well-evaluated tools to diagnose psychosocial distress and depression/anxiety in people with cancer in our community, and their family members and carers; and potential for the delivery of psychosocial interventions. The Cancer Helpline has unique broad access intervention capacity. The service has national coverage with uniform service standards; is promoted in national patient and clinician educational materials as a contact for evidence-based cancer support and information; national media coverage about cancer consistently uses the Cancer Helpline as a referral point for the public; the use of a tele-based delivery mode with a toll free contact number addresses geographical, disability, illness and cost barriers to access; the service is community based and accessible at any point in the illness continuum. Each year nationally over 30,000 patients and carers contact the Helpline. However, research is needed to extend the Helpline to include in depth psychosocial intervention; and to assess the relative efficacy of minimal contact approaches with individualised care. The present study will evaluate the relative efficacy and cost-effectiveness of these two approaches to psychosocial intervention for people distressed by cancer that are suitable for immediate population-based translation.

## Methods/design

### Study aims and hypotheses

The overall aim of the proposed study is to compare the efficacy and cost effectiveness of minimal contact self management materials vs. a tele-based psychologist delivered cognitive behavioural intervention in improving psychological outcomes for high distress cancer patients and carers over a 12 month period. Callers who contact The Cancer Council Cancer Helpline in Queensland and New South Wales over a five month time period will be screened for psychosocial distress and those callers with *elevated distress *will be randomised to one of the two study arms. The two study arms will comprise: (1) minimal contact self management vs. (2) five sessions of an individualised tele-based cognitive behavioural intervention delivered by a clinical psychologist.

Study hypotheses: It is hypothesised that 3, 6, and 12 months after recruitment:

1. Participants in both study arms will experience significant improvements in mental health compared to baseline levels including: reduced anxiety and depression; cancer specific distress; unmet psychological supportive care needs; and increased positive adjustment and quality of life.

2. Participants with *borderline anxiety/depression *who receive the minimal contact self management condition will experience significantly less anxiety and depression; less cancer specific distress, lower unmet psychological supportive care needs, higher positive adjustment and improved quality of life **by comparison **to participants with *high anxiety/depression *who receive the minimal contact self management condition.

3. Participants with *high anxiety/depression *who receive the individualised tele-based cognitive behavioural intervention condition will experience significantly less anxiety and depression; less cancer specific distress, lower unmet psychological supportive care needs, higher positive adjustment and improved quality of life **by comparison **to participants with *high anxiety/depression *who receive the minimal contact self management condition.

4. That from a health sector perspective, the individualised tele-based cognitive behavioural intervention is more 'cost-effective' compared to the minimal contact self management comparator for *high anxiety/depression participants*, **and **minimal contact self management is more cost-effective than the individualised tele-based cognitive behavioural intervention for *borderline anxiety/depression participants*; where $50,000 per QALY is taken as the benchmark for cost-effectiveness in Australia.

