### Participants

Study inclusion criteria will be that the patient/carer participants must: (1) be a cancer patient or carer ≥ 18 years of age who has called the Cancer Helpline for information or support (2) have a score of 4 or more on the Brief Distress Thermometer at the time of the Helpline contact (3) be able to read and speak English (4) have no previous history of head injury, dementia or psychiatric illness.

Callers who meet the selection criteria will be offered entry into the study by the Helpline operator at the time of the call; and once verbal permission to be contacted is obtained will be posted written consent and information forms. To minimise the period of time between calling the Helpline and randomisation into a support arm of the study, verbal consent to take part in the study will be obtained by project staff and audio taped prior to written consent. Baseline assessment will be conducted via telephone interview to prevent potential delays in receiving support. Participants will then be randomly allocated to receive either self management or the five session cognitive behavioural intervention. In all, 140 patients and 140 carers per condition will be recruited (allowing for a total of 280 people per treatment arm; 560 participants in total). On the basis of simulation work conducted by Raudenbush and Xiao-Feng [33], the present study, with 4 measurement periods and a total N of 560 will have power of at least .90 to detect a moderate longitudinal effect size. This sample size will allow for identification and investigation of subgroups of patients and carers (high vs. low/borderline distress) on the basis of their response to psychological intervention.

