### Statistical Analyses

The study is a multivariate, two condition randomized controlled trial with repeated measures across time. The analytic approach will be a multilevel model (MLM) in which measurement occasions (level 1) are nested within persons (level 2) and in which state/program differences are represented as a fixed effect at level 2 whose interaction with time represents differential adjustment and distress trajectories for the two groups. A key advantage of this approach is flexibility in dealing with missing data owing either to random or non-random attrition. Further, subgroups of patients and carers who respond differentially to the program will be identified using growth mixture modelling that is a related longitudinal procedure that identifies cases with similar distress and adjustment trajectories across time [43]. Jo's [44] results suggest that the proposed sample size will be sufficient to examine subgroups of responders.

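### Hypothesis 2 compares severity groups within one arm, so lower follow-up anxiety and depression in the borderline group is expected without any treatment effect

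*Protocol article*

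**What the plan says.** All from the protocol article.

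- **Study aims and hypotheses.** The list opens with "It is hypothesised that 3, 6, and 12 months after recruitment". Hypothesis 2 then says that participants with borderline anxiety/depression "who receive the minimal contact self management condition will experience significantly less anxiety and depression", along with better results on cancer-specific distress, unmet needs, positive adjustment and quality of life. The comparator is participants with high anxiety/depression "who receive the minimal contact self management condition". Both groups sit in one arm.
- **Same section, the other hypotheses.** Hypothesis 1 is a before-after statement for each arm. Hypothesis 3 compares the two arms on clinical outcomes, in high participants only. Hypothesis 4 compares the arms in both severity groups, on cost-effectiveness against $50,000 per QALY.
- **Background, community-based approaches.** The open question is "for which distressed patients a minimal contact approach would be efficacious, and for whom more in depth individualised approaches are necessary".
- **Background, mental health burden.** "The most powerful prospective predictor of longer term distress is current distress".
- **Participants.** "140 patients and 140 carers per condition will be recruited", which gives 280 per arm.
- **Study Integrity.** Randomisation is stratified by patient/carer and by state.
- **Statistical Analyses.** The multilevel model examines the interaction of group with time, and "subgroups of patients and carers who respond differentially to the program will be identified using growth mixture modelling".

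**The concern.** The groups in hypothesis 2 differ by construction on the first variable on which they are compared, and they receive the same treatment. A difference between them at follow-up therefore measures prognosis. The article itself supplies the premise that makes the result predictable, because it names current distress as the strongest predictor of later distress.

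The Background calls the matter of who benefits from minimal contact, and who needs more, critically important, and the trial is meant to feed directly into helpline practice. A near-automatic positive result on hypothesis 2 could be taken as evidence that borderline callers do well because of minimal contact, when the same pattern would appear had they received nothing.

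**Working it through.** **Plan's own figure.** The article gives no number for hypothesis 2. Its only power statement (Participants) is at least .90 for a moderate longitudinal effect with 560 people and 4 measurement periods. That calculation cannot be rerun, because no numerical effect size, variance components or alpha are given. Taking moderate as d = 0.5, a simple two-group test with 280 per arm has power above 0.999, which is compatible with the statement. Nothing below depends on it.

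**Assumptions (not in the article).**
- Severity groups are formed at baseline.
- Baseline gap between groups, G: 1.0-1.5 SD.
- Baseline-to-follow-up correlation, r: 0.4-0.6.
- Alpha 0.05 two-sided.
- Severity split 35/65 and retention 75%: 280 × 0.75 = 210 analysed, so about 74 v 136.

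**Step 1: expected follow-up gap with no treatment effect.** With equal SDs and a linear relation, gap = r × G.
- Lowest: 0.4 × 1.0 = 0.4 SD.
- Highest: 0.6 × 1.5 = 0.9 SD.

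**Step 2: probability that the level comparison is significant in the predicted direction.** Probability = Φ(gap/SE − 1.96), with SE = √(1/n₁ + 1/n₂).
- 74 v 136: SE = √(1/74 + 1/136) = 0.144.
- Gap 0.4: 0.4/0.144 = 2.77; Φ(0.81) = 0.79.
- Gap 0.6: 0.6/0.144 = 4.15; Φ(2.19) = 0.986.
- No dropout, gap 0.4: 98 v 182 gives 0.89; 140 v 140 gives 0.92.

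A valid one-direction test at this level would give 0.025.

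**Step 3: simulation of the minimal contact arm with no treatment effect.** Normal baseline X; follow-up Y = rX + error; 30%, 50% or 70% classed as high; Welch test; 2,000 replicates per setting; one time point.

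| r | Confirmed on levels, n = 280 | Confirmed on levels, n = 196 (70% retention) |
|---|---|---|
| 0.1 | 23-25% | 18-19% |
| 0.2 | 72-79% | 57-63% |
| 0.3 | 98-99% | 89-93% |
| 0.4 or more | about 100% | 99% or more |

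The simulated gap is 0.48-0.50 SD at r = 0.3 and 0.80-0.83 SD at r = 0.5 (n = 280). These rates exceed those in step 2 because splitting an unrestricted normal score at the median separates the groups by about 1.6 SD. The smaller gaps in steps 1 and 2 are the more cautious inputs. With a 50/50 split, and time points independent given baseline, significance at all three follow-ups occurs in 95% of null trials at r = 0.3 with n = 280, and in 81% with n = 196.

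**Step 4: the same comparison on change from baseline.** The expected difference in change is (r − 1) × G. Its size runs from 0.4 SD (r = 0.6, G = 1.0) to 0.9 SD (r = 0.4, G = 1.5), with the high group falling further. In the simulation hypothesis 2 is then confirmed in 0% of null trials, and high participants improve significantly more in 98-100%.

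**Step 5: the randomised alternative.** For the arm-by-severity interaction, SE = √(2/n_high + 2/n_borderline), with n counted per arm.
- Type I error by simulation (r = 0.5, 4,000 replicates): 4.9-5.3%.
- 50/50 split, no dropout: SE = √(2/140 + 2/140) = 0.169. Power is 84% for a 0.5 SD interaction and 43% for 0.3 SD.
- 30/70 split either way: SE = √(2/84 + 2/196) = 0.184. Power is 77% and 37%.
- Arm difference within borderline participants at d = 0.5: 99.9%, 98.7% or 90.0% when 30%, 50% or 70% are high.

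**The case against.** **Not all outcomes follow.** A reader might infer that hypothesis 2 as a whole is bound to be confirmed. That goes too far. The calculation covers anxiety and depression compared as levels, which is the literal wording. The other four outcomes depend on their correlation with baseline anxiety/depression, and positive adjustment, measured as posttraumatic growth, need not follow it. Read as change, the expected result reverses. This objection stands and limits the claim.

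**Hypothesis 4 is a randomised comparison in borderline participants.** It uses QALYs from the quality-of-life instrument, and Economic Analyses says that distress and unmet-needs data also enter the cost-effectiveness work. So one may not infer that the plan never compares the arms in this group, or that it says nothing about allocating care. What remains is narrower: no hypothesis compares the arms on clinical outcomes in borderline participants in their own right.

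**The model description is short.** One might infer that severity is absent from the multilevel model. The article condenses the model to a sentence or two, and a statistical analysis plan may hold the term, so its absence is no finding. Adding the term would not change the contrast that hypothesis 2 states.

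**Growth mixture modelling.** One might dismiss its classes as formed purely after randomisation. That is not accurate, since the four measurement periods include the pre-randomisation baseline. Even so, trajectory classes are not baseline-severity strata and do not supply the missing contrast.

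**The trial can answer the question.** Both severity groups are randomised. The defect lies in the stated hypothesis, not in the design or the data.

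**Conclusion.** The point holds for hypothesis 2 as worded. It is a non-randomised comparison of groups defined by the baseline level of its first outcome, so it carries no information on the effect of minimal contact or on whom it helps. For anxiety and depression as levels, the probability of confirmation with no effect is about 0.79 at the cautious end (0.4 SD gap, 74 v 136) and about 0.985 or more from 0.6 SD. The correlation, baseline gap, severity split, retention and alpha are all assumed. In the simulation, with its wider baseline gap, the conclusion holds down to r = 0.2 and weakens at r = 0.1.

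This should be fixed, but it does not undermine the trial. It concerns one of four hypotheses; hypotheses 3 and 4 rest on randomised contrasts; and recruitment, randomisation and measurement are unaffected.

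**What to change.** Restate hypothesis 2 as a randomised contrast with two parts:

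1. the arm-by-baseline-severity interaction, with severity taken from baseline BSI-18 anxiety/depression;
2. the arm difference with 95% CI within borderline participants at 3, 6 and 12 months.

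Keep the borderline-versus-high comparison within the minimal contact arm as a description of prognosis, labelled as such. A non-inferiority margin is needed only if the sponsor wishes to claim that minimal contact is not worse than the five-session programme. Hypothesis 2 makes no such claim now, and the repair does not require it.

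**Cost.** One reworded hypothesis and one model term, settled before unblinded analysis; no new data. The price is power: even with no dropout, an interaction of 0.3 SD would more likely be missed than found. The interval within borderline participants should therefore be reported alongside the interaction, and a non-significant interaction should not be read as equal benefit across severity.
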